## 8. Provisions to Monitor the Data to Ensure the Safety of Subjects

*This study involves no more than minimal risk study and this section is not required.* ☐ N/A

*The plan might include establishing a data monitoring committee and a plan for reporting data monitoring committee findings to the IRB and the sponsor.*

### Data and Safety Monitoring Plan

Title: Responsive Parenting, Sleep, and Rapid Weight Gain among African American Infants  
Grant # 1R01DK112874-01

#### I. Overview

##### *Purpose of the Study:*

The present study examines whether providing mothers of newborns with responsive parenting guidance during the first weeks of life to promote infant sleep and soothing can reduce rapid weight gain for African American infants born in low SES contexts, and also examines the risk and protective factors that may affect program efficacy.

##### *Adherence Statement:*

The Data and Safety Monitoring Plan (DSMP) outlined below for R01DK112874 will adhere to the protocol approved by the Augusta University IRB.

##### *Overall Framework for Safety Monitoring and Information to be Monitored:*

The data and safety monitoring plan (DSMP) for this intervention trial focuses on close monitoring of infant growth by the principal investigators (PIs) in conjunction with a Data Safety Monitor, along with prompt reporting of adverse events to the NIH/NIDDK and to the Institutional Review Board (IRB) at Augusta University. Because behavioral interventions aimed at reducing rapid weight gain could theoretically result in insufficient weight gain by study participants, infants' growth will

be closely monitored by the investigators, who will be overseen by the project's Safety Monitor, [name]. The decision to include a Data Safety Monitor instead of a Data and Safety Monitoring Board (as in the original proposal) was made in April 2018 in consultation with our Program Officer at NIDDK, [name]., based on NIDDK guidelines that a Data Safety Monitor is more appropriate for single-site clinical trials that are not masked and are minimal risk, as is the case in the current study.

## **II. Adverse Events**

In this study, an adverse event shall be defined as any detrimental change in the participant's condition, whether it is related to the study interventions, study outcomes, or to another unrelated illness. Adverse effects may be (a) unrelated to the study interventions, (b) potentially related to the study interventions, or (c) related to the study interventions.

### *Adverse Events Unrelated to the Study Interventions:*

Adverse events due to illnesses unrelated to study interventions may be grounds for withdrawal if the illness is considered significant by the study investigators or if the participant is no longer able to effectively participate in the study. A significant illness would be one that would compromise the child's ability to function normally and thrive, such as the diagnosis of a malignancy, illness characterized by growth problems, disease requiring ongoing and intensive treatment, and/or one requiring repeated hospitalizations or physician visits. Subjects experiencing routine, minor, self-limited acute illnesses that typically occur during infancy and do not affect long-term growth will not be recorded, and the child will continue to participate in the study. Examples of minor illnesses include acute otitis media, bronchiolitis, upper respiratory infections, urinary tract infections, and gastroenteritis. Medications for acute, self-limited illnesses such as those stated above will not be recorded, but chronic medication use (> 1 month) will be recorded.

Other adverse events that could affect growth include a milk-protein allergy, other food allergies, or physician-diagnosed gastroesophageal reflux disease (GERD) requiring medication. Surgical conditions such as intestinal malrotation and pyloric stenosis also would impact infant feeding and weight gain. Therefore, these will be recorded and if the study investigators determine that these conditions can affect long-term growth, the participant will be withdrawn from the study.

Documentation of an adverse event unrelated to study interventions that are not considered minor illnesses of childhood and those that can significantly affect growth will be recorded using Augusta University's interactive digital form for reporting adverse events

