## **7. Data and Specimen Management**

a. Describe the data analysis plan, including any statistical procedures:

☐  
N/A

Data analysis will be led by [name], who has expertise in the analysis of longitudinal data. [name]., Assistant Research Scientist and Statistician at CFR, will provide statistical support for the conduct of analyses. All primary statistical analyses will invoke the intent-to-treat paradigm, analyzing data based on randomized assignment. Missing data will be handled using full-information maximum likelihood methods, which use all available information to estimate parameters, making this approach more efficient and less biased than other methods when data are missing at random. All models considered allow for the inclusion of relevant covariates. Covariates to be considered in refining the analyses, in addition to those described in detail in the proposed analyses below, include demographic factors (e.g., maternal employment and hours worked, gestational diabetes), weight-related factors (e.g., maternal pre- pregnancy weight/BMI, gestational weight gain, maternal smoking), and intervention-related factors (e.g., implementation quality, coparent involvement in intervention). We will also examine (1) infant sex as a covariate, given different growth charts for boys and girls and (2) feeding mode as a covariate, given differences in weight gain between breastfed and formula-fed infants.

**Specific Aim 1: The Effects of Sleep SAAF on Infant Weight and Rapid Weight Gain.** In Specific Aim 1 the primary outcomes are infant weight and changes in weight. BMI is generally assumed to be the standard growth measure for assessing obesity-risk in children age 2 years and older, but there is not one universally accepted measure for children younger than age 2 years. Recent data suggests that infant BMI at age 2 months is more strongly associated with obesity at age 2 years than is weight-for-length. Accordingly, BMI z scores will be our primary outcome, but we will also consider models that examine a range of other weight outcomes, including weight for length z-scores, percentiles, and weight for age z-scores; we anticipate that change across different indices of weight gain will be highly correlated and lead to similar conclusions in tests of program impact as well as tests of potential moderators and the hypothesized mediational model.

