#### **Stopping Rules:**

As outlined above, we will continuously monitor adverse event rates in all participants. The study investigators, together with the Safety Monitor, will alert the IRB and the NIH/NIDDK if a greater

than or equal to 20% adverse event rate potentially due to study interventions should occur in the treatment group.

Any participant with a serious adverse event related to the study interventions will be discontinued from the study. Should insufficient weight gain be detected and the cause of this weight gain is related or potentially related to the study interventions as determined by Drs. [name] and [name], the participant will be discontinued from the study. Other non-minor concurrent illnesses or major changes in the family social environment would also lead to discontinuation as determined by the investigators.

As described in detail above, we will closely monitor rates of insufficient growth for individual infants and by study treatment group. In addition to individual level monitoring, the study statistician will analyze rates of insufficient growth by treatment group on a biannual basis if necessary. If there are significantly more children with inadequate growth in the intervention group at any point, these data will be presented to the Augusta University and UGA IRBs, the study's Safety Monitor, and the NIH/NIDDK so that a decision can be jointly made as to whether the trial needs to be suspended.

We acknowledge that there are other situations that could occur that might warrant stopping the trial, and these concerns will be discussed by [name], [name], and the Safety Monitor as needed.

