| 
b. If applicable, describe any procedures for orderly termination.
 
In the event that a subject is withdrawn from the research without their consent (whether due to unforeseen change in meeting inclusion criteria or an adverse event), all contact with subject will be ceased. Subjects will receive monetary compensation only for those appointments and study requirements met until the date of withdrawal. Any materials provided (bassinet, intervention materials) as part of the study procedures will remain with the subject. Only if agreed to at the time of consent, data collected for that subject dyad until the date of withdrawal will remain part of the study data and included in researcher analysis where possible.
 | 
 N/A
 |
| 
c. If applicable, describe procedures that will be followed when subjects withdraw from the research, including partial withdrawal from procedures with continued data collection.
 
In the event that subjects withdraw from the research, all contact with subject will be ceased. Subjects will receive monetary compensation only for those appointments and study requirements met until the date of withdrawal. Any materials provided (bassinet, intervention materials) as part of the study procedures will remain with the subject. Only if
                                                                                                                                                                                            | 
 N/A
 |

|                                                                                                                                                                                            |  |
|--------------------------------------------------------------------------------------------------------------------------------------------------------------------------------------------|--|
| agreed to at the time of consent, data collected for that subject dyad until the date of withdrawal will remain part of the study data and included in researcher analysis where possible. |  |
|--------------------------------------------------------------------------------------------------------------------------------------------------------------------------------------------|--|

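### Infants withdrawn after randomisation for growth-affecting illness are no longer measured, so their 16-week BMI z is missing for a reason tied to the outcome

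*Supplement*

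**What the plan says.** All references are to the latest protocol version in the Supplement.

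- **Randomisation** takes place at Home Visit 1, 7-10 days postpartum (Section 6(a)). Section 6(c) says that the study is not blinded.
- **Listed conditions** (Section 8, Adverse Events Unrelated to the Study Interventions). The medical ones are given as: "Other adverse events that could affect growth include a milk-protein allergy, other food allergies, or physician-diagnosed gastroesophageal reflux disease (GERD) requiring medication". The surgical ones follow: "Surgical conditions such as intestinal malrotation and pyloric stenosis also would impact infant feeding and weight gain". The consequence is that "if the study investigators determine that these conditions can affect long-term growth, the participant will be withdrawn from the study".
- **Other illness.** The same section is permissive: "Adverse events due to illnesses unrelated to study interventions may be grounds for withdrawal if the illness is considered significant by the study investigators". The Stopping Rules are firmer: "Other non-minor concurrent illnesses or major changes in the family social environment would also lead to discontinuation as determined by the investigators". Section 9(a) repeats this.
- **After withdrawal** without consent, including for an adverse event, Section 9(b) says that "all contact with subject will be ceased". Data already collected remain in the study only if this was agreed at consent.
- **Analysis** (Section 7(a)): "All primary statistical analyses will invoke the intent-to-treat paradigm, analyzing data based on randomized assignment". Missing data are handled by full-information maximum likelihood, which the plan justifies under missing at random. The primary outcome is BMI z at 16 weeks (Section 7(b)).

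**The concern.** Four features combine. The withdrawal happens after randomisation. Its criterion is an expected effect on growth, and growth is the outcome. The judgement is made by investigators who may know the arm. Measurement then stops before the primary endpoint.

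An intent-to-treat comparison needs outcomes on the infants as randomised, and this rule stops collecting them for a group selected on growth. Likelihood methods repair that only if the missing 16-week values can be predicted from what was observed earlier. For an infant withdrawn because growth is expected to change, that is doubtful. No sensitivity analysis for data not missing at random is described.

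Withdrawal could also differ by arm. The programme teaches parents how to read crying, hunger and fullness (Section 6(b)). If reflux or milk allergy tends to be diagnosed after complaints about crying and feeding, which is an inference and not a statement in the documents, diagnosis rates could differ between groups. What is at stake is a small bias of unknown sign in the primary comparison, and a growth-safety comparison by arm that lacks these infants' later weights.

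**Working it through.** **1. The plan's own figure.** Section 7(b) gives a detectable d of 0.34 at 80% power, two-sided 5%, with two groups of 175 and 10% attrition. A two-sample t-test gives:

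| n per group | detectable d | power at d 0.34 |
|---|---|---|
| 175 | 0.300 | 88.7% |
| 157.5 (175 less 10%) | 0.317 | 85.3% |
| 168.75 (375 × 0.9 / 2) | 0.306 | 87.6% |
| 135 | 0.342 | 79.5% |

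The stated 0.34 is not reproduced at 175 per group. The mismatch is conservative and is a separate matter. It is noted here only because it leaves some margin.

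**2. Loss of precision.** The documents give no withdrawal rate for these illnesses. I assume 3-8% of 375 dyads, which is 11-30 infants, and treat it as additional to the 10% attrition. That is itself an assumption. n per arm = 168.75 × (1 − loss).

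| extra loss | n per arm | detectable d | power at 0.34 | power at 0.40 |
|---|---|---|---|---|
| 0% | 168.75 | 0.306 | 87.6% | 95.6% |
| 3% | 163.7 | 0.311 | 86.6% | 95.0% |
| 5% | 160.3 | 0.314 | 85.9% | 94.6% |
| 8% | 155.25 | 0.319 | 84.8% | 94.0% |

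Power stays above 80% throughout.

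**3. Bias.** Let w1 and w0 be the shares withdrawn in the intervention and control arms, and D the amount by which withdrawn infants are lighter than the rest, taken as equal in both arms. Each arm's completer mean is too high by w × D, so the arm difference is shifted by (w1 − w0) × D.

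- Equal withdrawal of similar infants: shift 0.
- Gap of 2 points, D = 0.5 z: 0.02 × 0.5 = 0.01 z.
- Gap of 5 points, D = 1.0 z: 0.05 × 1.0 = 0.05 z.

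If the SD of BMI z is 1 (an assumption), these are 0.01/0.34 = 3% and 0.05/0.34 = 15% of an effect of 0.34.

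A worked case: 158 per arm before these withdrawals, 5% withdrawn in the intervention arm and 2% in control, D of 0.5-1.5 SD. The shift is 0.03 × D = 0.015-0.045 SD towards no effect. Power at d 0.34 is then 81-73%, and two-sided type I error 5.2-6.8%. If control infants are withdrawn more often, the sign reverses.

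These are unadjusted completer comparisons. They take no account of the 1-week weight covariate or of likelihood methods.

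**4. The texts side by side.** For illness outside the listed conditions, Section 8 makes withdrawal possible, while the Stopping Rules and Section 9(a) say it would follow. None of them separates leaving the programme from leaving measurement, and Section 9(b) ends both. Section 7(a) does not say how its intent-to-treat analysis treats infants whose outcome was never taken for this reason.

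**The case against.** The strongest reply is that nobody is removed from the analysis. Where consent allows, a withdrawn infant stays in the assigned arm with any 1-, 3- and 8-week measurements already taken. The illnesses are recorded and earlier weights are observed, so missing at random is not ruled out. This stands in part. A reader might infer that withdrawn infants are excluded from the analysis altogether, and the documents do not say that. What is lost is the later outcome. How far earlier data help the primary comparison is unclear, because the description of the 16-week model in Section 7(a) names only group and 1-week weight as terms.

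A reader might also infer that the trial becomes underpowered. At the plan's own d of 0.34 it does not. Nor can the loss be said to exceed the planned attrition: Section 7(b) assumes 10% over the study and excludes no cause, so these withdrawals may already be counted.

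The assumed rates may be high. Diagnosis alone does not trigger withdrawal under the rule for the listed conditions, minor illness does not count, and Section 3 already excludes neonatal conditions that significantly affect feeding. A 5-point gap at 3% overall would mean about 5.5% against 0.5%. That is fair, and it is why the size is shown only as a range.

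Finally, because the plan classes these events as unrelated, a reader might infer that withdrawal protects no one. The documents do not show that either way, and the clinical rule is not judged here. None of these replies explains why measurement has to stop.

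**Conclusion.** The point holds in limited form. Infants can be withdrawn after randomisation on an unblinded judgement about growth, and the 16-week BMI z is then not taken. That strains both the intent-to-treat statement and the missing-at-random basis.

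The likely size is small: about 0.01-0.05 z before adjustment if withdrawal differs by 2-5 points between arms and the infants are 0.5-1.0 z lighter, and nil if withdrawal and the growth of those withdrawn are alike in both arms. Power falls by about 1 to 3 percentage points at d 0.34 for 3-8% extra loss. Every rate is an assumption, and the direction of any bias is unknown. A claim that the result would be materially biased goes beyond the documents. This is a cheap improvement, worth making because the bias can be avoided at visits that are already planned.

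**What to change.** Reconcile Section 8 (Adverse Events Unrelated to the Study Interventions, and Stopping Rules), Section 9(a) and Section 9(b) with Section 7(a) by separating the end of participation in the programme from the end of measurement.

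- **Section 9(b):** state that infants withdrawn for illness under those rules are still weighed and measured at the remaining scheduled visits, above all at 16 weeks, unless the mother declines.
- **Section 7(a):** state that they are analysed as randomised. An optional sensitivity analysis leaves them out of both arms.
- **Sections 8 and 9(a):** bring the differing force of the wording on other illness into line.

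Whether and when programme sessions stop belongs to the sponsor's clinical rules, and nothing is proposed on that.

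**Cost:** protocol wording, and the consent text where it describes withdrawal. The visits are already scheduled. The downside is that a few infants with illness-affected growth add some variance.

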### *Adverse Events Related or Potentially Related to the Study Interventions:*

It is theoretically possible that behavioral interventions designed to prevent rapid weight gain during infancy could result in underfeeding by parents and insufficient growth. The NIH-funded studies that serve as the foundation for the current project did not find an association between study interventions and these adverse events. While the results of these previous projects are reassuring, weight status and growth will be closely monitored and evaluated at frequent intervals in the current project in order to monitor the study intervention for potential adverse events. In the current study, there are several ways a potential adverse event related to growth will be identified:

1. Weight-for-age below the 5th percentile using current CDC growth charts, based on WHO data from birth to 2 years.

2. Downward crossing of two major percentile lines on the WHO weight-for-age growth chart statistically evaluated as equal to or greater than a -0.67 Z-score change in order to provide a consistent measure across subjects.

Recognizing that growth monitoring is typically performed at all regularly scheduled primary care appointments, we will also ask mothers if their infant's PCP expressed concerns that the infant is demonstrating insufficient weight gain. In turn, the study team will determine if the infant meets one of these screening criteria above when assessed at study visits at 1 week, 3 weeks, 8 weeks, or 16 weeks.

During each study visit, home visit staff will assess weight. Within one week of the visit, the Project Coordinator will plot each child's growth on the CDC growth charts to allow for identification of potentially concerning growth patterns. [name] will be immediately alerted by the Project Coordinator to any concerning patterns (i.e., weight-for-age below the 5th percentile or downward crossing of two major percentile lines). After each child is closely evaluated, [name] will then contact the mothers by phone when necessary (i.e., when there is a potential adverse event related to infant growth), to discuss their infants' growth and whether a visit with the infant's primary care provider is necessary. If [name] is unable to reach the infant's mother and/or if the mother requests it, [name] will contact the infant's primary care provider directly. [name] will document these calls as they occur as a research note. [name] will review growth charts of all active study participants at least twice monthly.

For any individual child that meets initial screening criteria for growth concerns, numerous factors will be considered in determining whether the child's growth is problematic and/or related to study interventions. Examples of such factors include genetic potential based upon parental size, the participant's linear growth, feeding mode (breast milk vs. formula), and interval illnesses.

The study's informed consent document will include information indicating that the study team will communicate with the participant's PCP if necessary; all infants are required to have a PCP prior to discharge from the hospital and are expected to receive normal medical care (e.g., well-baby visits) throughout the study as is typical for infants. Doing so will allow for open lines of communication between the study team and the PCPs in the event of concerns related to growth. If either the primary care provider or the study investigators believe that it is possible that these growth patterns are a negative result from study participation, the child will be withdrawn from the study.

#### *Expected Rates for Failing Screening Criteria for Adverse Events Potentially Related to Study Interventions:*

Using standard population distributions, it is expected that 5% of children will be below the 5th percentile on the weight-for-age growth chart. For downward crossing of two major centile lines, it is expected that this will occur with some frequency given the well-established phenomenon of regression to the mean, which suggests that infants born at the higher percentiles have a higher probability of moving downward to the population mean. The results of our pilot study suggest that 15% of participants may experience this, and that will serve as the cut-off alarm value for this study. Combined, these two screening criteria allow for up to a 20% adverse event rate for those events related or potentially related to the study interventions.

